**Newly pooled data set and data included**
Participant data baselineCases of the intervention group at time point 0Cases of the wait-list control group at time point 1Participant data 10 weeks after intervention startCases of the intervention group at time point 1Cases of the wait-list control group at time point 2Participant data 24 weeks after intervention startCases of the intervention group at time point 2Cases of the wait-list control group at time point 3

##### Research Question 1

We will present the ITT sample’s baseline characteristics and test for detectable between-group differences. For continuous variables, mean, SD, median, minimum, and maximum values will be calculated. For categorical variables, frequencies (absolute and percentages) will be calculated.

To evaluate the effectiveness and efficacy of the 10-week access, we will create one difference score per group for each of our outcomes assessed at T0 and T1. Using a 2-sample *t* test, we will test whether significant differences exist between the 2 difference scores in the IG and WCG. We will perform this for the ITT and PP sample. If *P*<.05, Cohen *d* will be calculated.

##### Research Question 2

To evaluate long-term effectiveness and efficacy, we will use the pooled data set. To analyze the effect of time on our variables of interest, a repeated-measures ANOVA will be conducted for each of our outcomes. As only participants randomized to the IG will be assessed at 38 weeks after allocation, long-term efficacy within this group will be examined using an additional repeated-measures ANOVA.

Using a PP approach, we will examine the relationship between *app-based minutes of meditation* and each previously calculated difference score using the pooled data set. Linear regression will be performed to examine the relationship between the minutes of meditation and each outcome. The baseline scores of primary and secondary outcomes will be entered into the model as additional explanatory variables to control for individual differences before the start of the intervention.

##### Research Question 3

Using the pooled data set, to determine which variables are associated with adherence at 10 weeks and 24 weeks after intervention start, we will examine the correlations between the variable *frequency of meditation practice* and participants’ baseline characteristics, acceptability, and intensity of intervention use using the ITT sample. To assess adherence at 38 weeks after the intervention, analyses will be conducted using the ITT data set of the IG.

##### Research Question 4

Using the pooled data set, to determine which variables are associated with acceptability at 10 weeks after the intervention start and 24 weeks after the intervention start, we will examine the correlations between the variable of *perceived usefulness* (acceptability) and participants’ baseline characteristics and intensity of intervention use using ITT sample. To assess acceptability at 38 weeks after the intervention, analyses will be conducted using the ITT data set of the IG.

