#### Assignment of Interventions: Sequence Generation

Only individuals completing the baseline survey T0 were randomized to one of the study conditions. Randomization and allocation were performed by a third blinded research team member not involved in data analyses. Randomization was stratified by hospital and nursing school and job status (nurse or nursing trainee; 8 strata). Randomization was conducted using the website [28] (computer-generated random numbers), which generates a string of numbers comprising 1 (IG) and 2 (WCG) in random order. The length of the list was predefined and dependent on the number of participants per strata. The third blinded researcher combined each list of random numbers with the strata list of participants, thus randomizing each individual to either the intervention or control group. After the allocation, a research team member sent participants an email containing an access code for the app, links for web-based workshops, and a pickup location for workbooks.

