#### Outcomes

The German version of each questionnaire has been previously validated. All outcomes of interest consist of continuous variables based on self-report data. Our primary outcome will be perceived stress measured using the 10-item Perceived Stress Scale (PSS-10) [32]. Secondary outcomes will include sense of happiness (Likert scale) [33], life satisfaction (L-1) [34], mindfulness (Five Facet Mindfulness Questionnaire) [35], well-being (World Health Organization-Five Well-Being Index) [36], self-care (Hamburg Self-Care Questionnaire; only pacing scale) [37], pain intensity (numerical rating scale 0-10) [38], work-related sense of coherence questionnaire [39], burnout (Copenhagen Burnout Inventory; work-related burnout scale and client-related burnout scale) [40], job satisfaction (Warr-Cook-Wall Scale [41], modified by Cooper et al [42]), and work engagement (Utrecht Work Engagement Scale) [43].

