#### Sample Size

On the basis of the available literature on interventions similar to ours, we assumed a medium effect size (Cohen *d*=−0.67) in reducing stress measured by PSS-10 [44]. The sample size calculation was conducted for a 2-tailed *t* test with a significance level of α=.05 and a power of β=.80 (comparison between the IG and the WCG). Sample size calculations using the G*Power tool (Düsseldorf University) suggested that 72 participants (36 in the IG and 36 in the WCG) are needed to detect an effect size of 0.67. Assuming a dropout rate of 20%, 18 additional participants were required (45 per group).

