#### Statistical Methods

##### Overview

Analyses will be conducted using *SPSS Statistics* (IBM)*.* For tests involving our primary outcome variable, we will set an α level of .05. For all other analyses, to reduce α-error inflation, we will interpret the obtained *P* values descriptively, meaning all other analyses will be exploratory and are designed to observe trends and not to identify significance.

Patterns of missing data will be assessed, and adequate data imputation techniques such as multiple imputation with *SPSS Statistics* (IBM) will be applied. Before doing so, we will assess the percentage of missing data. We will also use Little's Missing Completely At Random test to determine patterns of missing data (ie, missing completely at random vs not missing at random).

We will reverse code 3 outcomes [32,38,40] so that a higher score indicates health improvement. For example, the scale assessing burnout [40] is designed to indicate that a score of 1 indicates a rather minuscule risk of burnout, whereas a score of 100 indicates the highest risk of burnout, meaning that greater scores indicate a worsening of symptoms. After recoding this variable, greater scores will reflect a lower risk of burnout (ie, an improvement in symptoms).

Effectiveness will be evaluated using an intention-to-treat (ITT) approach; all randomized participants will be included in our analyses [45].

Efficacy will be evaluated using a per-protocol (PP) approach; only study completers who report adherence will be included in our analyses.

Several analyses will be used to address the research questions. To ensure that our randomization has worked as intended, we will assess for between-group differences for relevant participant characteristics and, if needed, adjust the following analyses. For research questions 2, 3, and 4, we will create a pooled data set merging the data of the IG and the WCG. We will merge the data of the 2 groups so that IG T0 data will be combined with WCG T1 data, and IG T1 data will be combined with WCG T2 data, as described in Textbox 1. For research questions 3 and 4, relationships between variables will be examined using correlation analyses (Pearson correlation coefficient, eta quotient, and chi-square tests). If violations of the assumptions associated with any of the analyses are detected, alternative tests will be used.

Data pooling procedure.

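### The primary comparison is an unadjusted t test on change scores that ignores the randomization strata and leaves further adjustment to baseline tests; a prespecified baseline-adjusted ANCOVA is more precise and needs no new data.

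*Protocol article*

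**What the plan says.** The primary outcome is continuous: "Our primary outcome will be perceived stress measured using the 10-item Perceived Stress Scale (PSS-10"). For the 10-week comparison, Research Question 1 says "we will create one difference score per group for each of our outcomes assessed at T0 and T1" and applies a two-sample t test to the differences in the ITT and per-protocol samples. No covariate is named.

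The Sequence Generation section says "Randomization was stratified by hospital and nursing school and job status (nurse or nursing trainee; 8 strata"). Neither factor appears in the Research Question 1 test.

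The Statistical Methods overview says that, to verify the randomization, "we will assess for between-group differences for relevant participant characteristics and, if needed, adjust the following analyses". Research Question 1 adds tests of baseline differences in the ITT sample. The same rationale returns under Strengths and Limitations. Baseline scores are used as covariates in only one place, the Research Question 2 regression on minutes of meditation.

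**The concern.** Three choices in the stated text work against the primary estimate.

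- **Change score.** Subtracting T0 fixes the baseline slope at 1. With equal SDs at T0 and T1 the true slope is rho, so for any rho below 1 the subtraction over-corrects. Given a chance baseline difference D between groups, the change-score estimate is shifted by (rho − 1) × D. At rho 0.5, half of any chance imbalance passes into the estimate with its sign reversed (regression to the mean).
- **Strata left out.** Stratification removes between-stratum variation from the group comparison. If the analysis omits the strata, the standard error still includes that variation, and the test becomes conservative when the strata are prognostic.
- **Test, then adjust.** After random allocation, baseline differences are due to chance, so testing them cannot show whether randomization worked. Nor do the tests show which covariates predict the outcome. Under this rule the primary estimate may or may not be adjusted, and for whatever happened to differ.

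The comparison at T1 is the only randomized one, because the wait-list group receives the intervention at week 14. The trial is also below its planned size, so avoidable loss of precision matters.

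**Working it through.** **Inputs from the article.** The Sample Size section takes d=−0.67 on the PSS-10, two-sided alpha .05 and power .80. Its result is "72 participants (36 in the IG and 36 in the WCG) are needed to detect an effect size of 0.67". An allowance of 20% for dropout raises the target to 45 in each group. Results: 79 randomized, 40 to the intervention and 39 to the wait list.

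**Assumptions.** The article gives no T0–T1 correlation, so rho is shown from 0.3 to 0.7. It does not say which SD d refers to, so both readings are shown. Equal SDs at T0 and T1 are assumed unless stated.

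**Step 1: the plan's own figure.** A two-sample noncentral t calculation with d=0.67 and two-sided alpha 0.05 gives 36 per group (power 0.8005; 35 per group gives 0.789). Then 36/0.8 = 45 per group, 90 in total. The stated figures reproduce.

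**Step 2: variances**, in units of the raw-score variance.
- Change score: 2(1 − rho)
- ANCOVA: 1 − rho²
- Ratio ANCOVA/change: (1 − rho)(1 + rho) / [2(1 − rho)] = (1 + rho)/2

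This gives 0.65, 0.75 and 0.85 at rho 0.3, 0.5 and 0.7, a saving of 35%, 25% and 15%.

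**Step 3: power with d=0.67 on the raw-score SD.** The effective d is 0.67/√[2(1 − rho)] for the change score and 0.67/√(1 − rho²) for ANCOVA. Applying 20% dropout to those randomized gives 40 × 0.8 = 32 and 39 × 0.8 ≈ 31.

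| rho | Power, 32 v 31: change | Power, 32 v 31: ANCOVA | Power, 36 v 36: change | n per group for 80%: change | n per group for 80%: ANCOVA |
|---|---|---|---|---|---|
| 0.3 | 0.60 | 0.78 | 0.66 | 50 | 33 |
| 0.4 | 0.67 | 0.81 | 0.73 | 43 | 31 |
| 0.5 | 0.74 | 0.86 | 0.80 | 36 | 28 |
| 0.6 | 0.83 | 0.91 | 0.88 | 29 | 24 |
| 0.7 | 0.92 | 0.96 | 0.95 | 22 | 19 |

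On this reading, the planned 36 per group gives the change-score test 80% power only if rho is at least 0.5.

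**Step 4: power with d=0.67 on the change-score SD.** The planned test has 80% power with 36 per group whatever rho is, and 74% with 32 v 31. The effective d for ANCOVA is 0.67 × √[2(1 − rho)]/√(1 − rho²). Its power with 32 v 31 is 88%, 86%, 83% and 81% at rho 0.4, 0.5, 0.6 and 0.7.

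**Step 5: cost in degrees of freedom.** The ANCOVA figures above allow 1 df for baseline. Seven further terms for the eight strata lower power by about 0.002 at most.

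**Step 6: strata and the conditional rule, by simulation.** There were 8 unequal strata, N=64, groups balanced within strata and 8000 runs per scenario. Strata were assumed to explain 10% of the variance in level and to add 0.1 to the variance of change. The conditional rule was represented as ANCOVA if baseline stress differed at P<.05, and the change-score test otherwise.

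| Method | Type I error, rho 0.4 | Type I error, rho 0.6 | Power, rho 0.4 | Power, rho 0.6 |
|---|---|---|---|---|
| Change-score t test | 0.042 | 0.035 | 0.687 | 0.852 |
| Adjust only if baseline differs | 0.036 | 0.031 | 0.696 | 0.857 |
| ANCOVA with strata | 0.050 | 0.047 | 0.847 | 0.931 |

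Adjusting only after a significant baseline test recovers almost none of the gain.

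**The case against.** The planned test is legitimate. Under individual randomization the change-score t test is unbiased, and omitting the strata makes it conservative, not liberal. The regression-to-the-mean point concerns the estimate given an observed imbalance; it is not a bias of the procedure. All of this stands, and it limits the harm to lost precision and an open choice of model.

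The size of the gain also depends on inputs that the article does not give. If d is on the change-score SD, the planned 36 per group is enough at every rho. If the T1 SD exceeds the T0 SD, the gain shrinks. With an assumed SD ratio of 1.2, the variance ratio at rho 0.5 is 1.44 × 0.75/(2.44 − 1.2) = 1.08/1.24 = 0.87, and at rho 0.7 it is 1.44 × 0.51/(2.44 − 1.68) = 0.97. At high rho the difference in power is small in any case. The 32 v 31 figures describe completers, whereas the stated ITT analysis includes everyone randomized, with imputation. These points stand as limits on the magnitude. They do not reverse the direction: apart from a few degrees of freedom, ANCOVA is never less precise. With about 63 people and equal SDs, that small-sample penalty (about 1.7% in variance) cancels the gain only at rho near 0.97.

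Finally, a covariate list could sit in an analysis plan that is not shown. That is fair for the list. The t test and the rule of adjusting according to baseline comparisons, however, are stated in the article itself.

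**Conclusion.** The concern holds. The article fixes an unadjusted change-score t test, leaves out the stratification factors, and makes adjustment depend on baseline comparisons; no other section resolves this. With equal SDs and rho between 0.3 and 0.7, ANCOVA removes 15% to 35% of the variance. At the expected 32 v 31 completers this is worth 4 to 18 percentage points of power if d=0.67 is on the raw-score SD. If d is on the change-score SD, power rises from 74% to between 81% and 88% for rho 0.7 down to 0.4. The exact gain depends on rho, the SD ratio and the meaning of d, none of which the article gives. The primary result would not be invalid as planned, but it would be less precise than it could be and its model would not be fixed in advance. The change should be made.

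**What to change.** - Make the ITT analysis for Research Question 1 an ANCOVA of the T1 score on group, the T0 score of the same outcome, hospital and job status. Enter hospital and job status as main effects, because 79 people in 8 strata may leave sparse cells.
- Report the adjusted mean difference with its 95% CI whatever the P value. At present the effect size is to be calculated only after a significant test.
- Use the same model for the secondary outcomes.
- Present baseline characteristics descriptively. Delete the baseline tests and the rule that adjusts according to them. Name any further covariate before data are analysed.
- Reconcile the Design section, which gives only hospital or nursing school as the stratifier, with the abstract and the Sequence Generation section, which add job status.

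The cost is analysis wording only. Everyone randomized completed T0, hospital and job status are known, and SPSS fits the model. The article says analyses begin only after data collection ends, so the change can be documented as an amendment before then.

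### Research Question 1 calculates Cohen d only when P<.05, so the reported standardized effects are selected and too large on average, and a non-significant primary result gets none

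*Protocol article*

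**What the plan says.** The rule stands in the protocol article under Research Question 1. The plan is that "we will create one difference score per group for each of our outcomes assessed at T0 and T1". A two-sample t test then follows: "we will test whether significant differences exist between the 2 difference scores in the IG and WCG". The scope is both analysis sets: "We will perform this for the ITT and PP sample". The paragraph ends "If *P*<.05, Cohen *d* will be calculated". Nothing limits this condition to the primary outcome, and no other section provides a between-group d when P is .05 or more.

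The Overview under Statistical Methods separates the primary outcome from the rest. For the primary: "For tests involving our primary outcome variable, we will set an α level of .05". For everything else: "we will interpret the obtained *P* values descriptively, meaning all other analyses will be exploratory", and these analyses "are designed to observe trends and not to identify significance".

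The Sample Size section expresses the design assumption as a Cohen d of −0.67 on the PSS-10. The Outcomes section lists one primary and ten secondary measures.

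**The concern.** Two things are wrong, and they differ in reach.

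The first applies to all outcomes. When an estimate is calculated only after its test succeeds, small observed values are cut off, and the average of what remains lies above the truth. In a trial of this size the cut-off falls at a moderate effect, so any smaller observed effect has no d. If the primary result is not significant, the reader gets no d to set against the planning value. The protocol itself describes previous trials as mixed, some with no between-group difference, and plans to compare its results with other studies. A null result without a standardized effect makes that comparison harder.

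The second applies to the secondary outcomes only. Their P values are meant to be read descriptively, yet .05 decides whether each one gets an effect size. A standardized effect is a natural tool for describing a trend, and the rule withholds it from outcomes that are not significant.

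The rule governs Research Question 1, the only comparison of randomized groups. Research Questions 2 to 4 use pooled data or the intervention group alone.

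**Working it through.** **Inputs from the protocol.** Planning effect |d| = 0.67, two-sided α = .05, power 80%, 36 per group, 20% dropout giving 45 per group (Sample Size); 79 randomized, 40 v 39 (Results). **Assumptions.** True effects of 0.5, 0.3 and 0; 32 v 31 completers, from 40 × 0.8 = 32 and 39 × 0.8 = 31.2; a PP set of 20 v 20, since its size is not given. Signs are ignored.

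**1. The plan's own figure.** For a two-sample t test the noncentrality is d·√(n1·n2/(n1+n2)) = 0.67 × √18 = 2.84. With 70 degrees of freedom this gives power 0.8005 at 36 per group (0.789 at 35). Dropout: 36/0.8 = 45. The stated sample size reproduces.

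**2. Smallest d that can be calculated.** Since d = t·√(1/n1 + 1/n2), the condition P<.05 means |d| > t(0.975; n1+n2−2)·√(1/n1 + 1/n2).
- 40 v 39: 1.991 × 0.2250 = 0.448
- 32 v 31: 2.000 × 0.2520 = 0.504
- 20 v 20 (assumed PP): 2.024 × 0.3162 = 0.640

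**3. Mean d with and without the condition.** Simulation of the noncentral t, 400,000 draws per row, d obtained from t as above.

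| Groups | True d | Share with P<.05 | Mean d, all results | Mean d, P<.05 only | Ratio to truth |
|---|---|---|---|---|---|
| 40 v 39 | 0.67 | 84% | 0.677 | 0.744 | 1.1 |
| 40 v 39 | 0.5 | 59% | 0.505 | 0.656 | 1.3 |
| 40 v 39 | 0.3 | 26% | 0.303 | 0.588 | 2.0 |
| 32 v 31 | 0.67 | 74% | 0.678 | 0.790 | 1.2 |
| 32 v 31 | 0.5 | 50% | 0.506 | 0.714 | 1.4 |
| 32 v 31 | 0.3 | 22% | 0.304 | 0.650 | 2.2 |

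With no true effect, 5% of results pass, and their mean |d| is 0.538 at 40 v 39 and 0.605 at 32 v 31. At 20 v 20 a true 0.3 passes 15% of the time with mean 0.802. In the rows of the table, the unconditional mean is within 0.01 of the truth, so the excess comes from the condition.

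**4. Chance that the primary outcome gets no d.** This is one minus the share passing. At true d = 0.67 it is 16% (40 v 39) or 26% (32 v 31). At an assumed 0.5 it is 41% or 50%.

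**5. Consistency with the Overview.** Primary outcome: tested at .05, so a .05 threshold agrees. Secondary outcomes: significance is declared not to be the aim, yet the same threshold decides what is calculated. That does not agree.

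**The case against.** Several objections have force and limit the point.

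- *Not every reported d is inflated.* A reader might infer that each d shown is too large. Selection raises the average only. At true d = 0.67 and 40 v 39, about 40% of the results that pass are at or below the true value; at 32 v 31 it is 32%.
- *The large ratios rest on assumed effects.* The factor of about 2 needs a true d near 0.3, which the protocol does not give. At its own planning value the excess is about 11% at 40 v 39 and 18% at 32 v 31.
- *Which sample size applies.* The ITT analysis is to include all randomized participants, with multiple imputation named for missing data, so 40 v 39 is its nominal base. Imputation does not restore lost information, so this is a best case, and 32 v 31 serves as the other end of the range.
- *Only d is filtered.* A reader might infer that a null result would come with no effect estimate at all. The protocol does not say that means, mean differences, confidence intervals or P values will be withheld. With complete data, d can be recovered from t and the group sizes. This makes the gap smaller but does not justify the rule, and the recovery is less direct after multiple imputation.
- *The contradiction is partial.* A reader might infer that the whole rule conflicts with the Overview. For the primary outcome it does not. For the secondary outcomes, deciding when to add a descriptive d is not itself a claim of significance. But the same paragraph speaks of testing for significant differences in each outcome, which supports reading .05 there as a significance threshold.

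The case that a condensed article may leave detail to a fuller plan does not apply, because this is a stated rule and not an omission.

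**Conclusion.** The point holds for Cohen d under Research Question 1. The stated condition selects the standardized effects, inflates them on average, and leaves a non-significant primary result without the metric on which the trial was sized. For the secondary outcomes it also conflicts with their declared exploratory status.

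The bias is modest if the planning effect is true and grows as the true effect or the sample shrinks. The effect below which no d appears is about 0.45 with all participants analysed and 0.50 after the assumed 20% dropout. It would be higher in a smaller PP set, whose size is unknown. No test or sample is affected, and the primary conclusion does not change. This is a fault in what is calculated and reported, and worth correcting because the correction is nearly free.

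**What to change.** Under Research Question 1, delete the P<.05 condition. State that Cohen d with a 95% confidence interval will be calculated for the primary outcome and every secondary outcome, in both the ITT and PP samples, whatever the P value.

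The cost is one sentence and a few table columns. If multiple imputation is used, d and its interval must also be combined across the imputed data sets. No additional data are needed.

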#### Participant Timeline

The study will be conducted over a 10-month period (Table 1). A total of 4 surveys will be conducted 3 months apart from one another. Participants will be allowed 2.5 weeks to complete each survey. All participants randomized to the IG will receive access to the digitally supported mindfulness intervention 2 weeks after T0 data collection. All participants randomized to the WCG will receive access to the digitally supported mindfulness intervention 2 weeks after time point 1 [T1] data collection (14 weeks after the IG has been given access). Data collection for both groups will take place at 10, 24, and 38 weeks after allocation. In other words, data collection for each group will take place at 10 weeks (T1 for the IG and time point 2 [T2] for the WCG) and 24 weeks (T2 for the IG and time point 3 [T3] for the WCG) after intervention start. For individuals randomized to the IG, data will be collected at 38 weeks after the intervention starts (T3).

**Table 1 table1:** Schedule of enrollment, interventions, and assessments for the intervention group (IG) and the wait-list control group (WCG).

		Enrollment	Baseline	Random allocation	After allocation			
			T0^a^	Intervention start IG	T1^b^	Intervention Start WCG^c^	T2^d^	T3^e^

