Detection bias may occur as blinding of participants is not possible, given the nature of the study. Although the study design is not communicated to the participants, the participants are to be likely aware of which group they have been randomized to. There may be a risk of social desirability as the effects will be evaluated based on subjective reports, including the frequency and intensity of digitally supported mindfulness intervention use, and no biological parameters will be collected. To reduce detection bias, all questions were tested among members of the target group before the start of the study, and all outcome measures were validated in previous studies. Evaluations of the psychometric properties of our primary outcome, the PSS-10, in different countries report a Cronbach α of .78 to .91, with good test-retest reliability [57]. PSS-10 scores correlate significantly with cortisol levels and constitute an objective measure of cumulative stress [58]. We will also seek to reduce the risk of social desirability by informing participants of the pseudonymization and anonymous publication of the data and by conducting data collection without in-person contact. In addition, we will not use participant data collected via the app but will allow participants to report data collected by the app. We refrained from tracking app use and the duration of use for privacy reasons. Not tracking app use may increase rapport, as participants will not feel monitored while using the app. Finally, the item with which we assessed gender may present a limitation as the German language uses the same term for sex assigned at birth and gender identity; thus, we cannot be certain whether participants reported their sex or their gender.

Performance bias will be reduced by using a standardized intervention; however, COVID-19–related differences may occur, as the WCG will receive the intervention at a later time.

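### The long-term effectiveness and efficacy analysis is an uncontrolled change from baseline, so a calendar trend cannot be told apart from an intervention effect

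*Protocol article*

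**What the plan says.** Under Statistical Methods, Overview, the two groups are stacked by time since access: "IG T0 data will be combined with WCG T1 data, and IG T1 data will be combined with WCG T2 data". The data pooling box completes the rule: IG T2 goes with wait-list control group (WCG) T3 as the 24-week point. WCG T0 is not used.

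Under Research Question 2, this set serves to evaluate long-term effectiveness and efficacy: "To analyze the effect of time on our variables of interest, a repeated-measures ANOVA will be conducted for each of our outcomes". Neither a group factor nor a calendar-time term is mentioned. The 38-week point is a further repeated-measures ANOVA in the IG only, and the reason given is "As only participants randomized to the IG will be assessed at 38 weeks after allocation".

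Participant Timeline says otherwise: "Data collection for both groups will take place at 10, 24, and 38 weeks after allocation". There, the point reached by the IG alone is 38 weeks after intervention start.

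The Overview also says "For tests involving our primary outcome variable, we will set an α level of .05", and treats all other analyses as exploratory. The PSS-10 tests of Research Question 2 thus fall on the confirmatory side. The only planned between-group test is Research Question 1, on the T0 to T1 change. Strengths and Limitations concedes that "COVID-19–related differences may occur, as the WCG will receive the intervention at a later time".

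**The concern.** A test of time within persons asks whether scores moved, not why. Data collection runs from the end of September 2021 to the beginning of August 2022, in hospitals whose workload the Introduction describes as growing through the pandemic. Season, pandemic load, repeated surveys and regression to the mean (if people register when their stress is high) all act on the same scores as the intervention.

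The Abstract presents long-term follow-up as part of a rigorous evaluation of effectiveness and efficacy, and Strengths and Limitations says that an RCT identifies causal effects. For the 24- and 38-week results the planned analysis makes no use of the randomization. A long-term benefit could be reported when stress simply eased over the year, and a real one could be hidden if workload rose.

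**Working it through.** **The plan's own figure.** Sample Size uses a "2-tailed *t* test with a significance level of α=.05 and a power of β=.80" and "we assumed a medium effect size (Cohen *d*=−0.67) in reducing stress measured by PSS-10". A two-sample t test with d = 0.67 needs 35.96, so 36 per group (power 0.8005), and 36/0.8 = 45 per group with 20% dropout. Both figures reproduce. They cover Research Question 1 only.

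**What the pooled change measures with no intervention effect.** Let m(w) be the mean at week w after allocation, and take near-equal groups.
- 10-week change: [(m10 − m0) + (m24 − m10)]/2 = (m24 − m0)/2.
- 24-week change: [(m24 − m0) + (m38 − m10)]/2.

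A linear drift of 0.3 SD over 38 weeks appears as 0.3 × (24/38)/2 = 0.09 SD at 10 weeks and 0.3 × (24 + 28)/(2 × 38) = 0.21 SD at 24 weeks. The first interval also differs between the merged groups: 10 calendar weeks in the IG (T0 to T1) and 14 in the WCG (T1 to T2).

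**Rejection rate with no effect.** Inputs:
- 79 randomized (40 IG, 39 WCG; Results) and 20% dropout (Sample Size) leave 32 + 31 = 63.
- Assumed: within-person correlation ρ = 0.5, equal correlation between waves, and a drift of s SD per wave common to both groups.

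The ANOVA F statistic then has noncentrality λ = n Σ(m_j − m̄)²/(1 − ρ).
- Pooled: n = 63, three points, λ = 63 × 2s²/0.5, df 2 and 124.
- IG only: n = 32, four points, λ = 32 × 5s²/0.5, df 3 and 93.

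| Drift s per wave | λ pooled | Pooled rejection | λ IG only | IG-only rejection |
|---|---|---|---|---|
| 0 | 0 | 5% | 0 | 5% |
| 0.10 | 2.52 | 27% | 3.2 | 28% |
| 0.15 | 5.67 | 55% | 7.2 | 58% |
| 0.20 | 10.08 | 81% | 12.8 | 85% |

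Simulation of the same settings gives 27%, 55% and 80% (pooled) and 29%, 58% and 85% (IG only). With all 40 + 39 participants, a Greenhouse-Geisser correction and a linear drift of 0.3 SD over 38 weeks, simulated pooled rejection is about 34% at ρ = 0.5 and 55% at ρ = 0.7. In those runs the randomized change contrasts at T1 and T2 stay near 5%.

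**What a model on all data could recover.** Let δ10, δ24 and δ38 be the effects by time since access. The group differences have expectation δ10 at T1, δ24 − δ10 at T2 and δ38 − δ24 at T3, so all three are identified. With no group difference at T0 and ρ = 0.5, each baseline-adjusted difference has variance 0.75k and each pair has covariance 0.25k, where k = 1/32 + 1/31 = 0.0635.
- SE(δ10) = √(0.75k) = 0.218 SD.
- SE(δ24) = √((2 × 0.75 + 2 × 0.25)k) = √(2k) = 0.356 SD.
- SE(δ38) = √((3 × 0.75 + 6 × 0.25)k) = √(3.75k) = 0.488 SD.

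Power for 0.67 SD is Φ(0.67/0.356 − 1.96) = 47% at 24 weeks and Φ(0.67/0.488 − 1.96) = 28% at 38 weeks.

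**The case against.** The aims word Research Question 2 openly as change relative to baseline, and the article uses effectiveness and efficacy mainly to separate intention-to-treat from per-protocol. The sample size and the randomized answer belong to Research Question 1, which this point leaves untouched. All of that stands. It does not cure the label: the change is called long-term effectiveness and efficacy, the PSS-10 test has a confirmatory level, and the limitations do not say that the long-term analysis lacks a control.

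Four stronger readings are tempting but not supported.
- A reader might infer that the plan throws away treated-versus-untreated contrasts at T2 and T3. The WCG gets access at week 14, so these contrasts compare early with delayed access: 24 v 10 and 38 v 24 weeks since start.
- A reader might infer that any drift yields a significant result. At 0.1 SD per wave it does so in about a quarter of trials, and the staggered calendar windows can partly cancel non-monotone changes. The F test also has no direction: drift towards more stress would be significant without suggesting improvement.
- A reader might infer that repeated-measures ANOVA restricts the analysis to complete rows. The Overview plans multiple imputation and includes all randomized participants; complete cases are only the sensitivity analysis.
- A reader might infer that a mixed model would restore the long-term claim. It assumes that the effect by time since access is the same at every calendar wave, which the conceded COVID-19 differences put in doubt, and it is imprecise at this sample size.

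**Conclusion.** The point holds in this limited form. As written, Research Question 2 attributes within-person change to the intervention with no means of separating it from a monotone calendar trend, regression to the mean or survey effects. Under the assumed drifts of 0.1 to 0.2 SD per wave, with ρ = 0.5 and 63 completers, the nominal 5% error rises to about 27% to 80% (pooled) and 28% to 85% (IG only). The article gives neither drift nor ρ, so these rates show sensitivity and do not forecast the trial. The structural part needs no such assumption: no untreated group exists after week 14, and no between-group analysis is planned after T1.

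The statement about who is assessed at 38 weeks after allocation contradicts Participant Timeline. It is a wording error, but it is also the stated reason for analysing the IG alone at T3.

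**What to change.** 1. Report the pooled and IG-only ANOVAs as descriptive within-person change from baseline, not as effectiveness or efficacy, and state that there is no untreated control after week 14. This costs only wording.
2. As a supporting analysis, fit one linear mixed model to T0 to T3 of both groups, with fixed effects for calendar wave, time since access (0, 10, 24, 38 weeks) and strata, a participant random effect, and no group difference at T0. Describe the T2 and T3 contrasts as early versus delayed access. It needs no new data and one further model in SPSS. State its downsides beside it: the calendar-wave assumption, and SEs of about 0.36 SD at 24 weeks and 0.49 SD at 38 weeks, with about 47% and 28% power for d = 0.67.
3. Reconcile the 38-week sentence under Research Question 2 with Participant Timeline, under which both groups are assessed 38 weeks after allocation and only the IG is assessed 38 weeks after intervention start.
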